## Abstract

**Background:**

In low- and middle-income countries (LMICs), addressing the high prevalence of mental disorders is a challenge given the limited number and unequal distribution of specialists, as well as scarce resources allocated to mental health. The Mental Health Gap Action Programme (mhGAP) and its accompanying Intervention Guide (IG), developed by the World Health Organization (WHO), aim to address this challenge by training non-specialists such as general practitioners (GPs) in mental health care. This trial aims to implement and evaluate an adapted version of the mhGAP-IG (version 1.0) offered to GPs in 2 governorates of Tunisia (i.e., Tunis and Sousse), in order to uncover important information regarding implementation process and study design before country-wide implementation and evaluation.

**Methods/Design:**

First, a systematic review will be conducted to explore types and effectiveness of mental health training programs offered to GPs around the world, with a specific focus on programs implemented and evaluated in LMICs. Second, a cluster randomized controlled trial (RCT) will be conducted to evaluate the effectiveness of the implemented training based on the mhGAP-IG (version 1.0). Third, multiple case study design will be used to explore how contextual factors impact the successful implementation of the training and desired outcomes.

**Discussion:**

In Tunisia, an important need exists to further develop proximity health services and to address the growing mental health treatment gap. One solution is to train GPs in the detection, treatment, and management of mental health problems, given their strategic role in the healthcare system. This trial thus aims to implement and evaluate an adapted version of a training based on the mhGAP-IG (version 1.0) in Tunis and Sousse before country-wide implementation and evaluation. Several contributions are envisioned: adding to the growing evidence on the mhGAP and its accompanying guide, especially in French-speaking nations; building research capacity in Tunisia and more generally in LMICs by employing rigorous designs; evaluating an adapted version of the mhGAP-IG (version 1.0) on a sample of GPs; generating important information regarding implementation process and study design before country-wide implementation; and complimenting the trial results with implementation analysis, a priority in global mental health.

## Background

Health systems around the globe are facing enormous challenges, and these are particularly apparent in LMICs [1–4]. High prevalence of mental disorders, a reliance on limited and unevenly distributed specialists, and neglect of adequate investment in resources allocated to mental health have prevented between 76-85% of people living with mental health problems in LMICs from receiving any treatment [4–9]. This treatment gap, which is on the rise in LMICs, points to the dire need of developing proximity mental health services for a population “now among the most neglected and vulnerable throughout the world” [10].

International efforts are currently invested in reforms that build system capacity in primary and community-based settings for an number of reasons [8, 11–13]. First, there are proven user and system benefits of receiving care in such settings. These include: increased user and family satisfaction with services; reduced service costs; increased access to services for a wider population; and decreased stigmatized care [9, 14–17]. Second, current reforms target primary and community-based care because improvements in mental health system capacity do not require highly specialized professionals [7, 12, 18]. Contrary to wide-spread belief on delivering mental health services, most mental health problems can be effectively managed in non-specialized health settings by non-specialists through an approach called task-sharing [2, 19–27]. Task-sharing is defined as “moving the primary provision of the mental health intervention from mental health specialists (e.g., psychiatrists, psychologists, Master level providers) to lay counselors (i.e., limited to no mental health training or experience)” [25]. International efforts are assuming this approach because of its concordance with the realities of LMICs - it emphasizes the need to involve primary healthcare professionals and/or the lay workforce given the limited number and unequal distribution of mental health specialists [5, 18, 24, 25, 28].

GPs have been targets of many task-sharing initiatives worldwide because they are ideally placed in the healthcare system [29–31]. However, they often lack appropriate knowledge and skills to adequately detect, treat and manage mental health problems. To respond to this gap in knowledge, a number of mental health training programs targeting GPs have been developed and implemented worldwide. Such trainings contribute to health system reform in that “there is evidence that adequate training can reduce variations in provider behavior, improve fidelity, and ultimately increase the quality of service delivery” [32]. Developing and implementing mental health trainings that seek to build capacity and further integrate mental health into routine general practice has also been identified as a priority in global mental health [33].

It is important to note that questions regarding evidence on building mental health system capacity by offering training programs to non-specialized healthcare professionals, including GPs, often arise. First, findings are mainly from high-income countries (HICs) [7, 26, 34] and do not concord with the realities of LMICs due to differing culture and context, preventing the uptake of relevant and useful knowledge in these settings [34]. Therefore, generating appropriate and usable knowledge is an increasingly important research priority in global mental health [7, 26, 34, 35]. Second, most mental health training programs are focused solely ﻿on﻿ evaluating effectiveness or efficacy using experimental trials such as RCTs, which are known to disregard contextual factors that might influence the uptake and use of knowledge, practice-level changes, system-level changes, and sustainability of an implemented program [34, 36]. Therefore, implementation analysis is needed because﻿ it highlights how culture and context affect the successful implementation of an intervention within a dynamic environment, which can have a significant impact on desired training outcomes [36]. Last, most mental health training programs are not designed in the form of a ‘package,’ where training is complimented with guidelines that seek to develop mental health policies and systems [17, 26]. These guidelines are important because they can help decision-makers orchestrate and sustain reforms [7, 26, 37].

In 2008, the WHO launched the mhGAP in response to these gaps in evidence on building mental health system capacity. The Programme aims to train non-specialists in mental health detection, treatment, and management, all the while complimenting training with discussions around implementation, as well as system and policy development [26, 38]. In 2010, the mhGAP Intervention Guide (IG), currently in its second edition, was developed to encourage delivery of evidence-based interventions for what the WHO deems priority mental disorders [2, 39, 40]. The guide was developed by systematically searching the literature on ways to effectively treat and manage mental disorders in non-specialized settings by non-specialists [2]. Interventions included in the guide were also subject to international expert consultation [2].

The mhGAP-IG is the current mental health training of choice around the world for a number of reasons. Unlike previous mental health trainings, the evidence is based on findings specifically from LMICs, as well as expert opinion from researchers, decision-makers, and healthcare professionals working within these countries [26, 34, 39]. In addition, the mhGAP-IG was developed through international participatory consensus-based processes [39]. Participatory processes are particularly important when developing training interventions for mental health seeing as “the classification system for mental disorders that will be satisfactory for primary care must capture the complexity of the range of presentations of psychological problems in that setting” [39]. For the above mentioned reasons, the mhGAP-IG was chosen as the intervention for this trial.

The Tunisian Ministry of Health, in collaboration with the School of Public Health at the University of Montreal, the WHO office Tunisia, and the Montreal WHO-PAHO Collaborating Center for Research and Training in Mental Health (Douglas Mental Health University Institute), is interested in implementing an adapted version the mhGAP-IG in 2 governorates (i.e., Tunis and Sousse), in response to a country-wide health services reform that began in 2013. One of the main targets of this reform is to strengthen health system capacity by creating proximity health services [41, 42]. This reorganization aims to: 1) promote the use of multidisciplinary teams in primary care settings; 2) valorize general medical practice; and 3) equip primary care practitioners in effective patient management [42]. This reform is also discussed extensively to meet the needs of people living with mental health problems in Tunisia [41].

Implementing a mental health training based on the mhGAP-IG (version 1.0) thus comes at an opportune time during the health systems reform in Tunisia. Although Tunisia is equipped with mental health services, they are mainly provided in the capital (through the only standing and overcrowded mental health hospital in the country) and along the coastline (through psychiatric units within regional hospitals), making the distribution of resources uneven and impeding on equal access to services [43, 44]. In addition, Tunisia suffers from a shortage of mental health professionals, such as psychiatrists, psychologists, psychiatric nurses, and mental health social workers [41, 43] also echoed in many other LMICs. Shortages of mental health specialists in Tunisia force non-specialists such as GPs to receive between 30–40% of mental health consultations, despite their limited ability to adequately detect, treat, and manage mental health problems in primary care [41, 45].

## Objectives

This trial aims to implement and evaluate an adapted version of the mhGAP-IG (version 1.0) offered to GPs in 2 governorates of Tunisia (i.e., Tunis and Sousse), in order to uncover important information regarding implementation process and study design, before country-wide implementation and evaluation. The main objective of the trial is divided into 3 phases:

Phase 1 aims to answer the following research question by conducting a systematic review: 1) What types of mental health training programs offered to GPs have been implemented and evaluated, and are they effective? This review, which to our knowledge has not yet been previously conducted, will: 1) help us﻿﻿ gain a broader perspective on tested training outcomes, in order to inform this trial; 2) compliment already available findings on the mhGAP-IG; and 3) compare the effectiveness of a mental health training based on the mhGAP-IG (this trial) with previously implementing training programs in LMICs.

Phase 2 aims to answer the following research question by conducting a cluster RCT: 2) What is the potential value of building capacity in primary or community-based settings by training GPs in Tunis and Sousse (Tunisia) using the mhGAP-IG? Five specific modules from the mhGAP-IG (version 1.0) have been chosen by members of the Ministry of Health in Tunisia to reflect current and pressing needs: depression; psychosis; suicide/self-harm; alcohol use disorders; and drug use disorders. The main hypothesis of this cluster RCT is that the mental health training based on the mhGAP-IG will be clinically useful; will improve/increase GPs’ knowledge about disorders selected for training, attitudes towards mental illness, and perceived clinical self-efficacy; and will improve/increase rates of detection, treatment and management of mental illness. In addition, the cluster RCT will allow us to obtain crucial information on the design, namely the acceptability of delivering the mental health training as planned for the trial, as well as the estimated effect size and intra-cluster correlation (ICC) of a mental health training based on the mhGAP-IG. At the time this protocol was written and defended (June 2015), this information was not available.

Phase 3 aims to answer the following research question by multiple case study design: 3) How do contextual factors influence the successful implementation and expected outcomes of a mental health training based on the mhGAP-IG (version 1.0) offered to GPs in Tunis and Sousse (Tunisia)? This type of evaluation is referred to as Type III implementation analysis [36] and is currently a priority in global mental health [34].

## Methods/Design

### Phase 1: Conducting a Systematic Review

#### Search strategy and data collection

A systematic review will be conducted to explore the types and effectiveness of mental health training programs offered to GPs worldwide, with a specific focus on primary care in LMICs. To our knowledge, this is the first systematic review on the topic, and will be used to improve the training intervention offered to GPs in Tunis and Sousse. It will also compliment findings on the mhGAP-IG.

JS met with a librarian at University of Montreal to generate a search strategy for this review, which is currently underway. To answer the research question, the following databases are currently being searched: MEDLINE, PubMed, Embase, CINAHL, PsycINFO, and Web of Science. The main search terms used to generate the search strategy include: general practitioners; primary care; mental health; mental disorders; psychiatry; training programs; and education. Google will be used as a means to find grey literature. Once articles have been selected, reference lists will be searched for additional eligible articles. After indentifying the articles to be included in this review, key individuals in the field of capacity building by training GPs in mental health detection, treatment, and management will be contacted to validate findings and/or to obtain information on additional publications.

#### Study selection

Study eligibility criteria has been developed. These include: 1) academic and grey literature published from 1978 onwards; 2) articles written in English, French, and Spanish; and 3) study designs including RCTs, cluster RCTs, and quasi-experimental designs, to match our trial design. Studies will be excluded if they do not have a control/comparison group, and if they are descriptive or qualitative only.

#### Data analysis

Titles and abstracts of articles found using the search strategy will be reviewed. If they meet eligibility criteria, full texts will be obtained. Full texts will be included only if they meet eligibility criteria after review. Included texts will be reviewed for quality to deem if the training programs are effective.

Quality will be assessed using the *Quality Assessment Tool for Quantitative Studies* (1998) (http://www.ephpp.ca/tools.html) [46]. It was developed by *Effective Public Health Practice Project* (EPHPP) and specifically designed for use in public health. According to Jackson & Waters (2005) [47], this tool is considered adequate for analyzing articles that target interventions. Six content areas are included: allocation bias; confounders; blinding; data collection; as well as withdrawal and dropouts. Each of the content areas are rated as such: strong (3 points), moderate (2 points), and weak (1 point), for a maximum of 18 points per study analyzed. Content area scores are then averaged to provide the overall quality score [48].

Studies show that this quality tool has acceptable internal consistency and test-retest properties [47]. The *Quality Assessment Tool for Quantitative Studies* [46] is accompanied by a reviewer’s dictionary to ensure standardized use.

### Phase 2: Building mental health capacity by training GPs in Tunisia

The method section below follows the SPIRIT Guidelines.

### Participants, interventions and outcomes

#### Study setting

To assess the potential value of capacity building by training GPs in Tunis and Sousse using an adaptation of the mhGAP-IG (version 1.0), a cluster randomized controlled trial (RCT) with two arms (i.e., intervention and control) will be conducted. Tunis and Sousse have been chosen as they regroup the majority of the Tunisian population; they have access to the only standing mental health hospital in the country, as well as psychiatric units located in general hospitals; and in this area, there are substantially more resources allocated to mental healthcare (i.e., doctors, clinics, medication) than in other areas of Tunisia. Delegations (i.e., designated areas within the governorates) have been chosen as the clusters for this trial, seeing as health services are organized accordingly in Tunisia. There are 22 delegations in Tunis and 16 in Sousse, for a total of 38 delegations.

#### Eligibility criteria

The group of participants who will be recruited for this trial are GPs working within private or public institutions at the level of primary care in Tunis or Sousse. GPs will be recruited by identified clinicians working to promote continuing medical education in Tunis and Sousse. These clinicians, who work within private or public institutions at the level of primary care, have been selected by members of the Ministry of Health in Tunisia to be a part of this trial, as they have advanced knowledge and skills in the field of mental health, and they are mandated to encourage continuing medical education within their respective delegations. GPs will also be approached by 1 psychiatrist-trainer, as she works closely with GPs within the community.

To be included in the trial, GPs must meet the following eligibility criteria: 1) working within public or private institutions at the level of primary care in Tunis or Sousse; 2) having 5 or more years of clinical experience; 3) dedicating a minimum of 1 h per week to mental health; 4) being part of the *Conseil national de l’ordre des médecins de Tunisie* (CNOM), which is the GP order in Tunisia; and 5) being available when the training is scheduled. GPs will be excluded from the trial if they are retired or on sick leave; work in any other setting than in primary or community-based institutions; or do not dedicate any time to mental health or illness within their given work-week.

#### Interventions

The training intervention is based on an adapted version of the mhGAP-IG (version 1.0) developed by the WHO [2]. Instead of implementing all the suggested modules of the mhGAP-IG (version 1.0), 5 modules have been chosen for the purposes of this trial by members of the Ministry of Health in Tunisia: depression; psychosis; suicide/self-harm; alcohol use disorders; and drug use disorders. In addition to these modules, general principals of care as well as an introduction to the mhGAP will be presented.

Using the mhGAP Adaptation Guide developed by the WHO, the training modules and the accompanying training material (PowerPoint, trainer and participant guides) will be adapted to the local primary care context of the 2 governorates.

The training will be conducted by 3 Tunisian psychiatrists, trained in the proper use of the mhGAP-IG. The mhGAP training for participating GPs will take place one afternoon a week, over 5 weeks. A total of 17.5 h (3.5 h a week) is envisioned for the training modules, followed by a 2-h supervision session. During the supervision session, participating GPs will be invited to present mental health cases to the trainer-psychiatrists, engage in additional role plays, and review some of the material presented during the training sessions.

To improve adherence, participating GPs will be given an attestation signed by the President of the Committee for Mental Health Promotion in Tunisia, certifying that they have completed the training program.

#### Outcomes

Outcomes include GPs’ knowledge about disorders selected for training, attitudes towards mental illness, and perceived clinical self-efficacy in detecting, treating, and managing patients with the selected disorders.

#### Sample size

This trial will answer a number of important questions regarding study design, namely: What is the estimated effect size and ICC of a mental health training based on the mhGAP-IG? These parameters, to our knowledge, were not available at the time this protocol was written and defended (June 2015), and will thus make significant contribution to knowledge on the mhGAP-IG.

Following consultation with members of the Ministry of Health in Tunisia, the recommended average number of GPs to be recruited in the cluster (i.e., the delegation, many of which comprise the governorate) was suggested to be 15. While some studies using a cluster RCT to evaluate the effectiveness of a mental health training program offered to GPs in HICs do not report attrition [49–51], we are concerned that the evidence does not reflect the sampling realities in LMICs. For this reason, we aim to recruit 19 GPs per delegation, to be sure we account for a maximum of 20% attrition rate per cluster [52, 53]. Table 1 highlights the estimated sample size and number of clusters for the trial.

**Table 1 Tab1:** The sample size and number of clusters in the trial

PARAMETERS	#
n (total number of GPs)	722
# clusters (delegation)	38
n cluster (GPs on average per cluster)	19

Using the statistical software G*Power 3.1, the effect size can be calculated after data collection. Parameters will be set at: 1) test family: *t* test; 2) statistical test: difference between two independent means; 3) tail(s): two-tailed test; 4) type of power analysis: sensitivity; 5) alpha: 0.05; 6) power: 0.80; and 7) sample size (i.e., the total number of GPs) for control and intervention groups used in this trial. Once the effect size is found, the estimated ICC can be generated using the following formula, designed for cluster RCTs: *N =* N_sg_ (1 + (m-1) ICC), where:
*N =* number of participants in the trial (i.e., the total number of GPs);N_sg_ = number of participants in the trial, without considering clusters;m = number of participants in the cluster (i.e., the average number of GPs in the cluster);ICC = intra-cluster correlation (i.e., the correlation among GPs in the cluster).

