#### Statistical methods

All participants will be included in the analysis. This type of analysis is called intention-to-treat and is considered the best way to preserve the effects of randomization [53, 60]. Answers generated by questionnaires and surveys will be analyzed using SPSS Statistical Software (version 24).

T-tests on the difference in cluster means between the intervention and control groups [53] will be assessed for the questionnaires administered to the GPs. Two-tailed P values of less than 0.05 will be considered statistically significant. While the aforementioned t-tests take into account cluster level analysis, individual level analysis is discarded, which can underestimate the power of the analysis and generate misleading conclusions about the intervention [53, 61]. Adjustments can be made to the t-tests in order to account for individual level analysis. Campbell et al. (2000) [61] suggest that the t-test values (i.e., the differences between groups) should be divided by the square root of the design effect (i.e., 1 + (m-1) ICC). Two-tailed P values of less than 0.05 will be considered statistically significant. Individual level analysis will result in a higher significance level, compared with cluster level analysis [61].

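### The planned route to the effect size and ICC uses no outcome data, so it cannot estimate either of these two declared deliverables

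*Protocol article*

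**What the plan says.** The Objectives (Phase 2) list among the things to be learned from the cluster RCT its acceptability, "as well as the estimated effect size and intra-cluster correlation (ICC) of a mental health training based on the mhGAP-IG". The Sample size section repeats this as a research question, "What is the estimated effect size and ICC of a mental health training based on the mhGAP-IG", and counts the answer as a contribution to knowledge because neither parameter was available in June 2015.

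The same section fixes the method. For the effect size: "Using the statistical software G*Power 3.1, the effect size can be calculated after data collection". The settings are a t test with "statistical test: difference between two independent means; 3) tail(s): two-tailed test", then "type of power analysis: sensitivity; 5) alpha: 0.05; 6) power: 0.80", and finally the "sample size (i.e., the total number of GPs) for control and intervention groups used in this trial". The ICC follows: "Once the effect size is found, the estimated ICC can be generated using the following formula, designed for cluster RCTs". The formula is N = N_sg(1 + (m − 1)ICC), where N is the total number of GPs, N_sg is the number ignoring clusters and m is the average number per cluster. N_sg is given no value and no separate source. The article describes no other route to either quantity.

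The Statistical methods section first plans t-tests on cluster means. It then says that t values can be adjusted for individual-level analysis and "should be divided by the square root of the design effect (i.e., 1 + (m-1) ICC"). It does not say where that ICC comes from.

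**The concern.** A sensitivity analysis answers a design question: given alpha, power and the number of participants, what is the smallest effect the test would detect? The only thing it takes from the trial is the head-count in each arm. Useless training and excellent training would give the same figure, and GPs are treated as independent. The inflation formula is also a design tool. It converts an individually randomised sample size into a clustered one when the ICC is already known, and it contains nothing that measures how alike GPs in the same delegation are.

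Both figures are meant to inform country-wide implementation and evaluation. A later trial designed around an ICC of zero, or around a detectable effect mistaken for an observed one, would be wrongly sized. Within this trial, an ICC of zero makes the design effect 1, so the individual-level t-tests would go unadjusted.

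**Working it through.** **Inputs from the document.** There are 22 + 16 = 38 delegations, with 15 GPs wanted in each and 20% attrition. Alpha is 0.05 two-tailed and power is 0.80. No ICC and no allocation ratio are given, so equal arms (361 + 361 GPs, or 19 v 19 delegations) are an assumption here. Randomisation is in blocks of three, which cannot split 1:1 within a block, so a 2:1 split is shown as well.

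**1. The plan's own figure.** 15 / 0.80 = 18.75, rounded up to 19. Then 38 × 19 = 722, which agrees with Table 1. After attrition, 38 × 15 = 570. The sample-size arithmetic is not in dispute.

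**2. The G*Power step.** Solve for d in the two-sample t test (noncentral t) at the stated settings:

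| GPs per arm | d returned |
|---|---|
| 361 + 361 | 0.2088 |
| 285 + 285 | 0.2351 |
| 481 + 241 (2:1) | 0.2214 |

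Normal-approximation check for the first row: (1.960 + 0.842) × √(2/361) = 0.2085. Each value is fixed once the numbers per arm are known, whatever the questionnaires show.

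**3. The ICC step on the sequence described.** Rearranged, ICC = (N/N_sg − 1)/(m − 1). Deriving N_sg from the d of step 2, at the same alpha, power and allocation, undoes step 2 and returns the N that went in:
- N = 722, d = 0.2088: N_sg = 722, ICC = (722/722 − 1)/18 = 0.
- N = 570, d = 0.2351: N_sg = 570, ICC = (570/570 − 1)/14 = 0.
- N = 722 at 2:1, d = 0.2214: N_sg = 722, ICC = 0.

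Taking N_sg by its definition, as the number in the trial with clusters ignored, also gives N_sg = N and ICC = 0.

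**4. Other ways of filling in N_sg.** Rounding d to 0.21 gives N_sg = 714 and ICC = (722/714 − 1)/18 = 0.0006. Rounding 0.235 to 0.24 at N = 570 gives N_sg = 548 and ICC = 0.003. Mixing recruited and retained numbers gives (722/570 − 1)/18 = 0.015. These are artefacts.

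Substituting an observed effect, which the text does not specify, gives these illustrative values (N = 722, m = 19):

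| Observed d | N_sg | (722/N_sg − 1)/18 |
|---|---|---|
| 0.2 | 788 | −0.005 |
| 0.3 | 352 | 0.058 |
| 0.5 | 128 | 0.26 |
| 0.8 | 52 | 0.72 |
| 1.0 | 34 | 1.12 |

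The number rises with the training effect, passes 1 and carries no information on clustering.

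**5. Comparison with an estimator that uses the data.** One-way ANOVA ICC within arm, simulated with 38 delegations of 19 GPs, 500 runs per setting. For true ICCs of 0, 0.02, 0.05, 0.10 and 0.20, the mean estimates were 0.00, 0.019, 0.049, 0.10 and 0.20, whether the true effect was 0 or 0.5 SD. The planned route gives d = 0.209 and ICC = 0 in every one of these cases.

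**6. Consequence for the individual-level t-tests, if this ICC is used there.** Assume a true ICC of 0.05. At m = 19 the design effect is 1 + 18 × 0.05 = 1.9. The unadjusted test then has type I error 2[1 − Φ(1.96/√1.9)] = 2[1 − Φ(1.422)] = 15.5%. At m = 15 the design effect is 1.7 and the error is 13.3%.

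**7. Minimum detectable effect with clustering included.** With 19 v 19 delegations (36 df), m = 15 and assumed ICCs of 0.01, 0.05 and 0.10, the design effects are 1.14, 1.70 and 2.40 and the detectable effects are 0.26, 0.31 and 0.37 SD.

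**The case against.** Four points can be made for the plan.

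- **The text does not say how N_sg is obtained.** This stands. An ICC of exactly zero is what the described sequence and the literal definition give, but rounding or mixed inputs give small non-zero values, and an observed effect gives something else again. It does not rescue the method, because none of these readings estimates the ICC.
- **Inference is protected by the cluster-mean t-tests.** This also stands. A reader might infer that an ICC of zero removes the clustering correction from the whole analysis. The Statistical methods section does not support that: its first analysis works on cluster means and needs no ICC. Only the additional individual-level tests use the design effect, and it is a reasonable inference, not a statement, that they would take the ICC from the Sample size section.
- **The plan will still produce results from the data.** Correct. A reader might infer that the trial yields no data-based effect at all, but comparing cluster means does produce between-arm differences. What fails is the quantity that the Sample size section calls the effect size, together with the ICC.
- **The article is a summary and its wording is permissive; a statistical analysis plan may give the detail.** This has little force here. The point is not missing detail: software, type of analysis, settings and formula are all stated, and a later plan that follows them inherits the error.

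**Conclusion.** Wrong as written. The effect size obtained this way is a minimum detectable effect under individual randomisation: about 0.209 SD for 722 GPs or 0.235 for 570 with 1:1 allocation, and 0.221 for 722 at 2:1. The ICC is zero on the sequence the text describes and is not a valid estimate on any reading.

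This must be corrected because the two quantities are declared deliverables of the trial, not because its cluster-level comparison is at risk. The type I error of about 15.5% (13.3% at m = 15) applies only to the individual-level t-tests. It is conditional on this ICC being used there and on a true ICC of 0.05, which is an assumption because the document gives none.

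**What to change.** Replace the G*Power and formula steps in the Sample size section as follows.

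1. **Effect size.** For each outcome, report the observed difference between arms at T-2, when the control group is still untrained. Give it also divided by the pooled SD, with a 95% CI that respects clustering.
2. **ICC.** For each outcome, estimate it from the between- and within-delegation variance within arm, with a 95% CI. The one-way ANOVA estimator is enough; a mixed model would also serve but would have to be added to the plan.
3. **Link to the analysis.** State in Statistical methods that the design effect uses the ICC estimated in step 2 for that outcome.
4. **Sensitivity result.** If kept, call it a minimum detectable effect and include the design effect and the assumed ICC and split, as in step 7 of the working.

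The cost is wording before analysis. The data are already to be collected and no further GPs are needed. The stated detectable effect becomes less favourable: 0.26 to 0.37 SD over assumed ICCs of 0.01 to 0.10, compared with 0.235 for the same 570 GPs when clustering is ignored.
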